### Clinical outcomes analysis

The primary outcome measure is the transformed global health status subscale score of the QLQ-C30 at 12 weeks from randomisation. Analysis of the primary outcome will be carried out using an analysis of covariance with adjustment for baseline values to compare between groups. Primary and secondary analyses will be carried out on the intention-to-treat (ITT) population.

As a secondary analysis of the primary outcome a mixed-effects regression model will be used, which will account for the repeated measures over time.

Secondary outcomes: for all patient reported secondary outcomes mixed-effects regression models will be used, taking account of the repeated measures. Overall survival from date of randomisation will be analysed using Kaplan-Meir curves and the Log-rank test.

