### Study design and setting

This is a multi-centre randomised, non-blinded, parallel group controlled trial comparing early referral to a specialist palliative care team for regular early SPC versus standard care. A summary of the study design is illustrated in Figure 1. Study recruitment commenced in March 2014. It is planned that this trial will be conducted in up to ten centres in England and Scotland.

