### Randomisation and blinding

Following completion of the baseline assessment, eligible patients and their carers will be minimised with a random element in a 1:1 ratio between the intervention and control groups using a centralised randomisation database managed by the Oxford Respiratory Trials Unit (ORTU), Oxford, UK.

Participants will be minimised according to:1) centre, 2) plan for chemotherapy (yes/no), 3) ECOG PS (0 or 1) and 4) histological sub-type (epithelioid versus non-epithelioid (biphasic, sarcomatoid, not defined)).

Due to the nature of the intervention it is not possible to blind participants or the immediate research team to the allocated intervention. Interventions and outcome assessments will therefore be un-blinded. Data analysis will be performed in a blinded fashion.

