### Sample size

Assuming a population mean of 55 and a common standard deviation of 22 in GHS/HRQoL for mesothelioma patients[20], a sample size of 78 patients in each arm will be required to detect a 10-point difference in the mean scores between the two groups, with a power of 90% at a 5% two-sided significance level, assuming an autocorrelation of 0.25.

UK National Lung Cancer Audit data demonstrate approximately 6% mortality at 12 weeks for PS 0 to 1 patients - therefore, we will factor a 10% dropout before the primary endpoint is reached at 12 weeks. Therefore, the sample size allowing for a power of 90%, a 5% two-sided significance level, a minimal clinically important difference (MCID) of 10 units in the GHS/HRQoL and a dropout of 10% (n = 16) is 174 patients.

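### The stated primary ANCOVA leaves out the minimisation factors; if they are prognostic, its standard error is too large and its test conservative

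*Protocol article*

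**What the plan says.** Under *Randomisation and blinding*, the protocol article says that "eligible patients and their carers will be minimised with a random element in a 1:1 ratio between the intervention and control groups". The factors are "1) centre, 2) plan for chemotherapy (yes/no), 3) ECOG PS (0 or 1) and 4) histological sub-type", with subtype reduced to epithelioid versus all others. *Study design and setting* adds: "It is planned that this trial will be conducted in up to ten centres in England and Scotland".

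Under *Clinical outcomes analysis*, the primary outcome is the global health status score at 12 weeks, and its model is given in one sentence: "Analysis of the primary outcome will be carried out using an analysis of covariance with adjustment for baseline values to compare between groups". The same section plans mixed-effects models for the repeated measures and a log-rank test for survival, and lists no covariates for either. No section puts the minimisation factors into any model.

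*Sample size* rests on one correlation term: "with a power of 90% at a 5% two-sided significance level, assuming an autocorrelation of 0.25". Since that is the only covariate information used there, the baseline values of the primary model are most naturally read as the baseline global health status score.

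**The concern.** Minimisation removes most of the chance difference between arms in the four factors. The treatment estimate therefore varies less from one possible allocation to the next than it would under simple randomisation. A model without the factors does not know this. It leaves their contribution in the residual variance and computes a standard error as though they had been free to fall unevenly. If the factors matter for the outcome, the reported standard error exceeds the true one, the interval is too wide, and the test rejects a true null less often than 5%. Precision that the design has already secured goes unused.

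The article gives some reason to expect the factors to matter. *Inclusion criteria* separates PS 0 from PS 1 by the presence of symptoms, and *Background* links fatigue, dyspnoea and pain to worse global quality of life. *Background* also says chemotherapy goes to the fittest patients. *Control arm* leaves palliative referral to local practice, which may vary by centre.

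**Working it through.** **Inputs from *Sample size*.** "Assuming a population mean of 55 and a common standard deviation of 22 in GHS/HRQoL for mesothelioma patients"; difference 10; 78 per arm; two-sided 5%; power 90%; autocorrelation 0.25; 174 patients after 10% dropout (156/0.9 = 173.3, rounded up to 174).

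**The plan's own figure.** n per arm = 2(1.960 + 1.282)² × 22² × (1 − r²)/10².
- No baseline adjustment: 102.
- 0.25 read as r (1 − r² = 0.9375): 96; 78 per arm then gives about 83% power.
- 0.25 read as r² (r = 0.5, 1 − r² = 0.75): 77, or 78 with the t distribution (power 90.3%).

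The stated 78 reproduces only on the last reading. Which was meant is a separate question, so both are carried through.

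**Closed form with perfect balance.** Let R² be the share of the 12-week variance left after baseline that the four factors explain. Then true SE = reported SE × √(1 − R²), and actual size = 2Φ(−1.96/√(1 − R²)).
- R² = 5%: reported SE 1/√0.95 = 1.03 times the true one; size 4.4%.
- R² = 10%: 1.05 times; size 3.9%.
- R² = 20%: 1.12 times; size 2.8%.

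**Simulation with imperfect balance.** Minimisation has a random element and patients drop out, so balance among those analysed is not perfect. For each r, 2,500 trials of 174 patients were simulated. Assumptions not taken from the documents: ten centres of equal expected size; the favoured arm assigned with probability 0.8; binary factors with prevalence 0.5, 0.6 and 0.35; the four factors contributing equally; dropout of about 10% at random. The adjusted model used three binary terms and nine centre indicators.

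| r | R² | True SE, baseline only | Reported SE, baseline only | Ratio | Type I error, baseline only | Power, baseline only | Power, factors added | Power forgone (points) |
|---|---|---|---|---|---|---|---|---|
| 0.5 | 0% | 3.028 | 3.059 | 1.01 | 5.0% | 90.32% | 90.04% | −0.3 |
| 0.5 | 5% | 2.971 | 3.059 | 1.03 | 4.4% | 90.72% | 91.16% | 0.4 |
| 0.5 | 10% | 2.910 | 3.059 | 1.05 | 4.1% | 91.12% | 92.68% | 1.6 |
| 0.5 | 20% | 2.784 | 3.060 | 1.10 | 3.2% | 92.28% | 95.28% | 3.0 |
| 0.25 | 0% | 3.410 | 3.414 | 1.00 | 5.2% | 83.28% | 82.88% | −0.4 |
| 0.25 | 5% | 3.350 | 3.417 | 1.02 | 4.4% | 83.56% | 84.32% | 0.8 |
| 0.25 | 10% | 3.283 | 3.418 | 1.04 | 4.0% | 84.24% | 86.16% | 1.9 |
| 0.25 | 20% | 3.142 | 3.421 | 1.09 | 3.2% | 84.92% | 89.80% | 4.9 |

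With the factors added, type I error was 4.8% (r = 0.5) and 5.0% (r = 0.25) at every R². The simulation error of one type I rate is about √(0.05 × 0.95/2500) = 0.44 points, so the 5% rows alone would not prove the effect; the closed form gives the same direction and nearly the same size. At 20% the simulated effect is smaller than the closed form (size 3.2% against 2.8%), as imperfect balance would lead one to expect.

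**The case against.** **The article is condensed and the SAP is not shown.** The model sentence does not say that baseline values are the only covariates, and a fuller list could stand elsewhere. This holds in part. A reader might infer that the investigators have decided to exclude the factors; the text does not support that. It does, however, name the covariate adjustment for the primary test, and that adjustment does not match the allocation. For the mixed-effects models no covariates are given at all, so their absence there is no fault; carrying the terms over is for consistency.

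**The harm depends on an unknown.** Entry is restricted to PS 0 to 1, and baseline global health status may absorb much of what the factors predict. At R² = 0 there is no harm, and the adjusted model is worse by 0.3 to 0.4 points of power. This stands: the direction is certain only if the factors are prognostic, and the size cannot be taken from the documents.

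**The error is on the safe side.** The estimate is unbiased and the test conservative, so a positive result would remain valid. This stands in full.

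**No planned power is lost.** A reader might infer that the omission takes the trial below its design power, or worsens an existing shortfall. Neither is supported. In the table, baseline-only power rises with R² on both readings of 0.25. What is forgone is a gain that the sample size never counted on, and whether 78 per arm reaches 90% depends on the reading of 0.25, not on this omission.

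**Conclusion.** The point holds in conditional form. The stated primary model does not reflect the minimisation. If the four factors predict the 12-week score beyond baseline, its standard error is overstated and its test conservative. Under the assumed range of 0 to 20% of residual variance, the effect runs from nothing to a type I error of about 3.2%, a standard error about 10% too large, and 3 to 5 points of power forgone against the adjusted model. At 5% it is very small. It does not threaten the validity of a positive finding. It is an improvement that should be made because it is nearly free, not a defect that undermines the trial.

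**What to change.** State the primary model in *Clinical outcomes analysis* as a regression of 12-week global health status on arm, baseline global health status, planned chemotherapy (yes/no), ECOG PS (0 or 1) and histological subtype (epithelioid or not), with centre as a random intercept given up to ten sites. Carry the same terms into the mixed-effects models. Fix this before the outcome data are analysed, so that the covariates are not chosen afterwards.

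The cost is wording only. All four factors are recorded at randomisation, and neither the sample size nor data collection changes. The model spends three fixed-effect degrees of freedom and one variance component out of about 156 patients. Even the more expensive version simulated, with nine centre indicators (twelve added terms), cost no more than 0.4 points of power when the factors explained nothing.

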**Methods:**

This multicentre study is an non-blinded, randomised controlled, parallel group trial. A total of 174 patients with a new diagnosis of malignant pleural mesothelioma will be minimised with a random element in a 1:1 ratio to receive either 4weekly regular early specialist symptom control care, or standard care. The primary outcome is health related quality of life for patients at 12 weeks. Secondary outcomes include health related quality of life for patients at 24 weeks, carer health related quality of life at 12 and 24 weeks, patient and carer mood at 12 and 24 weeks, overall survival and analysis of healthcare utilisation and cost.

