## Background

Malignant pleural Mesothelioma (MPM) is an incurable cancer of the lining of the lung caused by exposure to asbestos. Prior to controls on asbestos exposure introduced in the 1970s, industrial asbestos exposure was widespread in the United Kingdom (UK), although a much larger workforce involved with lagging and construction continued to be exposed until the early 1980s[1]. Imports of asbestos to the UK only ceased in 1999[2].

The UK now has the highest death rate from MPM in the world[1] and predictions forecast this figure increasing up to 2015 and possibly 2020[3–5]. More precise predictions are hampered by the long lag time between exposure and disease manifestation of at least 30 to 40 years[6]. The projected lifetime risk of MPM for a UK male born in the 1940s is 0.59%, or approximately 1 in 170 of all deaths[3].

There is no cure for mesothelioma. Prognosis is poor, with a median survival of between 8 and 12 months, although long survivors are recognised[7]. A previous study examining health related quality of life (HRQoL) in MPM patients receiving chemotherapy has demonstrated that 92% of patients have 3 or more physical symptoms at presentation[8]. Fatigue (94%), dyspnoea (89%), appetite loss (87%) and pain (85%) were the most common, with fatigue, dyspnoea and pain associated with a worse global HRQoL. Aggressive treatment strategies to prolong life include combinations of surgery, radiotherapy and chemotherapy, but remain controversial with no sound evidence base. At present, the fittest patients with mesothelioma will be offered chemotherapy with palliative intent, which has been shown to improve survival by two to three months in clinical trials[9]. For less fit patients, best supportive care remains the mainstay of treatment. The fundamental aim of palliative care is to achieve the best quality of life for patients and their carers. This is achieved with specialist symptom control and provision of psychological, social and spiritual (not necessarily religious) support.

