## Discussion

This study will inform clinicians of a potentially novel way to care for patients with this high symptom-burden disease for which there is no cure, and limited treatment options. The additional aspect of healthcare resource utilisation analysis will allow further interpretation of the results and may inform clinicians and policy-makers as to a more complete understanding as to the implications of this intervention.

In the design of the RESPECT-MESO study we have attempted to allow as pragmatic an approach as possible, to ensure as wide as possible external applicability of the results, within the confines of ensuring internal validity and appropriate scientific rigor. One of the central difficult decisions made was to only include subjects with an ECOG PS of 0 to 1. This was based on UK National Lung Cancer Audit data demonstrating approximately 24% mortality at 12 weeks for PS 2 patients with mesothelioma. Such attrition would have significantly increased the challenge of obtaining adequate data for the primary endpoint at 12 weeks. Nevertheless, UK data demonstrate that 70 to 80% of patients with mesothelioma have a PS of 0 to 1 at the time of diagnosis[24–27], so our approach will allow the inclusion of the majority of cases at presentation.

One of the additional key challenges encountered in the setup of the study was developing the necessary links with SPC services. This has been addressed by early engagement with SPC teams and offering SPC team leads the opportunity of taking on local co-principal investigator roles. When screening potential host sites for suitability we have used a feasibility assessment focusing on the availability of SPC services and asking sites to nominate both respiratory and SPC leads for the study.

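### The plain log-rank test planned for overall survival ignores performance status and histology, on which allocation is minimised; this can cost a few points of power on a secondary outcome

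*Protocol article*

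**What the plan says.** The Clinical outcomes analysis section of the protocol article gives the survival method in one sentence: "Overall survival from date of randomisation will be analysed using Kaplan-Meir curves and the Log-rank test". It names no strata, covariates or regression model. It also does not use the word unstratified. The same section specifies baseline adjustment for the primary outcome and mixed-effects models for the patient-reported secondary outcomes.

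Under Randomisation and blinding, patients are "minimised with a random element in a 1:1 ratio between the intervention and control groups", and the factors are listed: "Participants will be minimised according to:1) centre, 2) plan for chemotherapy (yes/no), 3) ECOG PS (0 or 1) and 4) histological sub-type". Histology enters as two levels, epithelioid against all other types. On the number of sites, Study design and setting says: "It is planned that this trial will be conducted in up to ten centres in England and Scotland".

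Survival is a secondary outcome; the abstract lists it after "patient and carer mood at 12 and 24 weeks, overall survival and analysis of healthcare utilisation and cost" begins with mood. The article gives no hazard ratio, event number or power for it. The total of 174 is set by global health status at 12 weeks.

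**The concern.** Minimisation makes the arms more alike on PS and histology than simple randomisation would. If those factors predict death, the difference between arms varies less from trial to trial than the plain log-rank variance assumes. The test then rejects too rarely under no effect and has less power than a test that uses the factors. Unmodelled prognostic variation also pulls the marginal hazard ratio towards 1.

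What is at stake is information the trial already collects. The Background notes that an earlier lung cancer trial of early palliative care reported longer survival without having planned or powered for it. Readers will therefore look at this pre-specified survival comparison, and the trial is small for it.

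**Working it through.** **The plan's own figure.** There is none for survival. The sample size follows from the primary outcome: 78 / 0.9 = 86.7, so 87 per arm and 174 in total. That total is used below.

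**From the article.** N = 174; 1:1 minimisation with a random element on four factors; up to ten centres (10 used). On survival the Background says: "Prognosis is poor, with a median survival of between 8 and 12 months" (10 months used).

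**Assumed, because the article gives no value.** Exponential survival; 24 months' accrual with at least 6 months' follow-up; 30% non-epithelioid, 60% PS 1, 60% with planned chemotherapy; probability 0.8 of the balancing allocation; treatment hazard ratio 0.65; and all prognostic hazard ratios.

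**Test.** Z = Σ(a − p) / √Σp(1 − p), summed over deaths. Here a is 1 if the death is in one given arm and 0 otherwise, and p is that arm's share of those at risk. The plain test takes p over all patients. The stratified test takes p within the four PS × histology groups. The null is rejected if |Z| > 1.96.

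**Results.** 6000 trials per row under no effect (Monte Carlo SE 0.3 points) and 3000 under hazard ratio 0.65 (SE 0.9 points). Losses are taken before rounding.

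| Assumed HR, histology / PS | Size, plain | Size, stratified | Power, plain | Power, stratified | Power lost by plain test |
|---|---|---|---|---|---|
| 1 / 1 | 4.7% | 4.6% | 60.1% | 58.4% | −1.7 |
| 1.5 / 1.3 | 5.0% | 5.7% | 59.3% | 59.4% | 0.2 |
| 2.0 / 1.4 | 4.1% | 5.1% | 55.7% | 58.7% | 3.0 |
| 2.5 / 1.7 | 3.6% | 5.3% | 51.4% | 57.3% | 6.0 |
| 2.0 / 1.4, and 1.5 for no chemotherapy | 3.8% | 4.7% | 53.6% | 56.7% | 3.0 |

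A repeat under four-factor minimisation gave a size of about 4.0% to 4.2% for the plain test and a loss of about 2 to 7 points between 2.0/1.4 and 2.5/1.7. It gave a loss of about 1 point at 1.5/1.3, and a cost of about 2 points from stratifying when neither factor matters. A simpler model with exact balance in the four groups, PS hazard ratio 1.5 and longer follow-up gave power of 61.6% against 65.9% (histology 2.0) and 61.4% against 67.7% (histology 2.5), losses of 4.3 and 6.3 points.

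**Check on the simulation.** Schoenfeld's formula is power = Φ(½√d·|ln HR| − 1.96). With about 105 deaths and HR 0.65: ½ × 10.25 × 0.431 − 1.96 = 0.247, and Φ(0.247) = 59.8%. The simulated value with no prognostic factors is 60.1%.

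**Why not all four factors.** PS × histology × chemotherapy × ten centres makes 2 × 2 × 2 × 10 = 80 strata, or 174 / 80 ≈ 2.2 patients each. Power falls to 31% to 35% across the rows above. Adding chemotherapy alone to PS × histology costs 1.2 to 2.0 points.

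**Scale against the event count.** For HR 0.7 the formula gives 43% power at 100 deaths and 65% even if all 174 patients die. For 80% power, 4 × (1.960 + 0.842)² / (ln 0.7)² = 247 deaths are needed, more than the trial has patients.

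**The case against.** The strongest reply is that this is a condensed article, the analysis plan is not shown, and strata for a secondary outcome usually belong there. That stands in part: the absence of a Cox model or of the word stratified is not itself an error. But the article does name a test, and in ordinary usage that name means the unstratified one. The same section states adjustment for the primary outcome. The point is about improving a named method.

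A reader might infer strong prognostic effects from the article's mortality figures: about 6% at 12 weeks for PS 0 to 1, against "approximately 24% mortality at 12 weeks for PS 2 patients with mesothelioma". The documents do not support that step. PS 2 patients are excluded, the balancing factor is PS 0 against 1, and the 6% pools those two levels. No survival effect of histology is given either.

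It is also fair that a marginal log-rank comparison is a legitimate target, that a conservative test cannot inflate false positives, and that the number of deaths limits the survival result far more than stratification does. All of this stands, and it sets the level of the point.

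**Conclusion.** The point holds as an optional efficiency improvement on a secondary outcome that the trial was not sized for. Against a test stratified by PS and histology, the plain test loses about 0 to 7 points of power across assumed histology/PS hazard ratios from 1.5/1.3 to 2.5/1.7, at a treatment hazard ratio of 0.65. Its size is about 3.6% to 4.2% from 2.0/1.4 upwards, with no detectable conservatism at 1.5/1.3. Part of the power gain is simply the size returning to about 5%. If neither factor is prognostic, stratifying costs about 2 points.

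A reader might go further and conclude that power is certainly lost, or that the survival test is invalid. Neither follows. The loss depends on prognostic strength within PS 0 to 1, which the documents do not give, and the plain test remains valid. The 12-week quality-of-life conclusion is not affected.

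**What to change.** Test overall survival with a log-rank test stratified by ECOG PS (0 or 1) and histological subtype (epithelioid or not). Do not add centre to the strata. Report a hazard ratio with 95% CI from a Cox model adjusted for PS, histology and planned chemotherapy, described as a conditional estimate. Keep the Kaplan-Meier curves for display. Fix this before survival is compared by arm. If the analysis plan already says so, only the wording needs to agree.

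The cost is analysis wording. The three factors are needed for allocation and so are known for every randomised patient. The statistical price is the roughly 2 points of power given up if PS and histology turn out not to be prognostic.

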#### Missing data

To minimise total and item non-response, we will perform monthly telephone interviews for quality of life data and clinic appointments for 12- and 24-week questionnaires with the research team. If missing data are substantial (>10%) then multiple imputation techniques will be used for the primary outcome to account for missing data under the missing at random assumption.

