**Control**											
Patient	QLQC-30, LC13, EQ-5D, GHQ-12	X				X			X		
	Telephone interview (QLQC-30, LC13)			X	X		X	X			
Carer	GHQ-12, SF-36, FAMCARE-2	X				X			X		X

EOT = end of trial;EQ-5D = EuroQol-5D;FAMCARE-2 = family satisfaction with advanced cancer care 2; GHQ-12 = General Health Questionnaire-12; LC13 = lung cancer supplement;,QLQ-C30 = Quality of Life Questionnaire Core 30;SF-36 = Short Form 36;SPC = Specialist Palliative Care.

After consent, the following information will be collected from all patients at the baseline assessment prior to randomisation: patient demographics, date and type of diagnostic pleural procedure, histological subtype of mesothelioma, current performance status (from MDT) and co-morbidities, previous treatments and pleural procedures, treatment plan, medication use, patient HRQoL and mood questionnaires (EORTC-QLQC30, EORTC-LC13, EQ-5D, GHQ-12), neutrophil and lymphocyte values at time of diagnosis, International Mesothelioma Interest Group (IMIG) stage of disease[19] at time of diagnosis (staging data will only be collected from selected sites). From the designated main carer, the following information will be obtained: carer current health utilisation, work status (full or part time, retired), HRQoL and mood questionnaires (SF-36, FAMCARE-2, GHQ-12).

At 12 weeks (primary end point) and 24 weeks, patients and carers from both the intervention and control groups will be seen in clinic and the following information will be documented: patient history including recent treatments and hospital/healthcare utilisation, medication use, patient HRQoL and mood questionnaires (EORTC-QLQC30, EORTC-LC13, EQ-5D, GHQ-12). For carers: healthcare resource utilisation, work status (and days of work missed as appropriate), carer HRQoL and mood questionnaires (SF-36, FAMCARE-2, GHQ-12). Clinic visits will ensure better quality, more complete data for the primary endpoint.

Telephone consultations with patients in both the intervention and control group will be performed at 4, 8, 16 and 20 weeks to obtain the following information: recent treatments and hospital usage, medication use, HRQoL questionnaires (EORTC-QLQC30, EORTC-LC13).

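### The imputation rule for the primary outcome turns on a 10% cut-off equal to the planned dropout, and below it the primary ANCOVA makes no use of the week 4 and 8 scores

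*Protocol article*

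**What the plan says.** All references are to the protocol article.

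- **Clinical outcomes analysis:** the primary analysis is an ANCOVA of the week 12 global health status score, adjusted for baseline, in the intention-to-treat population. A mixed-effects model for the repeated measures is planned as a secondary analysis of the same outcome, with no condition on how much is missing.
- **Missing data:** "If missing data are substantial (>10%) then multiple imputation techniques will be used for the primary outcome", and this is done "to account for missing data under the missing at random assumption".
- **Sample size:** "we will factor a 10% dropout before the primary endpoint is reached at 12 weeks". The basis given is "approximately 6% mortality at 12 weeks for PS 0 to 1 patients". The total is reached with "a dropout of 10% (n = 16) is 174 patients".
- **Study visit schedule:** "Telephone consultations with patients in both the intervention and control group will be performed at 4, 8, 16 and 20 weeks". QLQ-C30 is among the questionnaires given at those calls, so global health status is measured at weeks 4 and 8 in both arms.

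**The concern.** How missing week 12 scores are handled in the headline analysis is decided by the data, at a cut-off placed where the design expects the trial to land. A difference of one patient decides whether patients without a week 12 score enter the primary analysis through imputation or contribute nothing.

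Below the cut-off, a baseline-adjusted ANCOVA on observed scores is unbiased only if loss depends on nothing relevant beyond baseline and arm. In a disease with a median survival of 8 to 12 months, loss may well follow deterioration already visible at weeks 4 and 8. If that loss is also unequal between arms, the treatment contrast is shifted. Unequal loss is possible here: the trial is unblinded, and only one arm has scheduled four-weekly specialist visits. The rule as written contains nothing that responds to imbalance.

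**Working it through.** **1. The plan's own figures.** The Sample size section needs 78 per arm, so 156 evaluable. 156 / (1 − 0.10) = 173.3, rounded up to an even total of 174, as stated. The implied loss is 174 − 156 = 18, and 18/174 = 10.3%, just above the trigger. The dropout count printed in the same section is 16, which is 10% of 156 (15.6); 16/174 = 9.2%, just below it. The plan's two versions of its expected loss therefore fall on opposite sides of the cut-off.

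**2. Where the switch occurs.** 10% of 174 is 17.4. So 17 missing (9.8%) gives no imputation and 18 missing (10.3%) gives imputation.

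**3. Chance of triggering imputation.** With X ~ Binomial(174, p), the chance is P(X ≥ 18):

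| True missing rate p | P(imputation) |
|---|---|
| 6% | 0.02 |
| 8% | 0.16 |
| 10% (planned) | 0.48 |
| 12% | 0.78 |
| 15% | 0.97 |

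At the planning value the rule is close to a coin toss.

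**4. Imbalance below the cut-off.** If the 10% refers to the whole trial, 17 missing split 14/87 (16.1%) v 3/87 (3.4%) does not trigger imputation, although Fisher's exact p is 0.009.

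**5. Size of the bias below the cut-off.** This was simulated, 3,000 trials per setting.

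- From the protocol: 87 per arm, mean 55, SD 22.
- Assumed: no true effect; equal correlation r between all visits (0.25 or 0.5); in each arm, the patients lost are those with the lowest sum of week 4 and week 8 scores plus random noise (SD 15).
- Compared: ANCOVA on observed week 12 scores with baseline only, and the same ANCOVA after missing week 12 scores were filled by regression on arm, baseline, week 4 and week 8. The regression fill stands in for the point estimate from multiple imputation.

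| Missing, control v intervention | r | Bias, observed-case ANCOVA | Bias, imputation with weeks 4 and 8 |
|---|---|---|---|
| 14 v 3 | 0.25 | −1.02 | 0.00 |
| 14 v 3 | 0.5 | −1.35 | 0.01 |
| 12 v 5 | 0.25 | −0.68 | −0.03 |
| 12 v 5 | 0.5 | −0.88 | −0.04 |
| 8 v 8 | 0.25 | 0.00 | −0.01 |
| 8 v 8 | 0.5 | −0.07 | −0.06 |

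The sign follows the arm that loses more. Here control loses more, so its observed mean is too high and the intervention looks worse; the reverse split would reverse the sign. The standard deviation of the estimate was about 3.4 points (r = 0.25) or 3.0 (r = 0.5) under either method.

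**6. Deaths.** Expected mortality of about 6% against 10% total loss makes deaths about 6/10 of the planned loss, or roughly 0.06 × 174 = 10 patients. The simulation does not cover them: it treats every lost patient as having a week 12 score that could have been observed.

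**The case against.** The rule is prespecified and numeric, so it leaves the analyst little discretion. It matters most when realised loss is near 10%; at 6% or 15% the outcome is nearly certain. The wording is also compatible with imputation followed by the same ANCOVA, so the model itself need not change. All of this stands, but near 10% is where the design places the trial.

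Three stronger readings are tempting, and the document does not support them.

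- *The plan prescribes a complete-case analysis and an overall threshold.* It uses neither term. Both are natural readings, since no other handling is given below 10% and no arm is mentioned. On imbalance between arms the rule is silent; it does not rule out attention to it. The counting rule and the imputation variables may stand in a fuller document.
- *The week 4 and 8 scores are thrown away.* They enter the mixed model for this same outcome at any level of missingness. They are absent only from the ANCOVA that carries the primary result.
- *The bias is 2 points, a fifth of the MCID.* That comes from taking a 20-point deficit in those lost and 5% v 15% loss: 20 × (0.15 − 0.05) = 2. It is the bias of an unadjusted difference in means on assumed inputs. It does not show what survives baseline adjustment or what imputation would recover.

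A last objection stands in full: methods that assume missing at random do not settle quality of life after death, and deaths are more than half of the planned loss.

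**Conclusion.** The point holds in a limited form. The trigger coincides with the planned dropout, so at a true 10% loss the handling of the primary outcome has about a 48% chance of going one way and 52% the other. Below the trigger, on the natural reading, the primary analysis uses only baseline and week 12 scores although relevant intermediate scores exist, and the analysis that uses them is secondary.

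The likely damage is modest: about 1.0 to 1.3 points against an MCID of 10 under a deliberately uneven 14 v 3 split with loss driven by interim scores, and about 0 when loss is equal between arms. Nothing in the document shows that unequal loss is expected. The case for change is that the threshold serves no purpose when an analysis without one is already planned on data already being collected.

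**What to change.** Remove the 10% threshold and prespecify one primary approach at any level of missingness, before any comparative data are seen. Either:

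- make the already planned mixed model primary, using the scores up to week 12 (including weeks 4 and 8), with the treatment contrast at week 12; or
- keep the ANCOVA, always run after multiple imputation by arm with the week 4 and 8 scores as auxiliary variables.

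Keep the observed-case ANCOVA as a sensitivity analysis. State how deaths before week 12 are treated in the primary contrast, and add a sensitivity analysis for them, since neither option resolves them.

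The cost is a change of wording and slightly more analysis work. No new data are needed and N stays at 174.
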